### Secondary Analyses

#### Does the Untire App Improve Quality of Life Significantly After 12 Weeks of App Access?

To examine the treatment effect of the app on QoL, the data derived from the 2 QoL questions will be analyzed following the same analytic procedure as described above in the main analyses.

#### What Are the Reach, Costs of Online Recruitment, and What Is the Uptake and Usage of the Untire App (Study)?

To explore the number of participants reached using Web-based social media campaigns, we will use the number of Web-based advertisement link clicks, leading to the study landing page. To determine the costs of recruitment, the number of link clicks will be compared with the budget spent on social media campaigns. We will calculate the total costs of recruitment, the costs per person who clicked the link, and the costs per person that completed the baseline (study) assessment. To examine how many participants completed the assessments, activated the app, and used the app in the first 12 weeks of the study, percentages and count data will be used. Log data will indicate how many participants activated their unique access code, the number of days a participant has been active in the app, and the number of activities performed.

#### Which Factors Moderate, and Which Factors Mediate the Hypothesized Effect of the Intervention?

Moderating factors (ie, age, gender, and country) of the intervention effect of the app on CRF and QoL will be explored as a three-way interaction (time×condition×moderator variable) using GLMM as described above to gain insights into whether the intervention effect varies among different groups of participants, for example, patient with cancer versus survivor. Moreover, we will examine via longitudinal mediation analysis, whether levels of mindfulness, physical activity, depression, sleep, pain interference, and fatigue catastrophizing mediate the hypothesized effect of the intervention.

### Sample Size

Sample size calculations for the primary outcome of fatigue showed that we needed to include 164 participants with complete 12-weeks measures in the intervention and the control group (total N=328) to detect a between-group difference in change from baseline to 12 weeks with a minimal effect size of η^2^=0.10 (alpha=.05, 1−beta=.95). The sample size was calculated using the simplest between/within-group comparison (F tests—repeated measures analysis of variance [with within-between interaction]) in G*Power 3.1. With the inclusion of 820 participants (410 intervention participants; 410 control participants) and an estimated drop-out of (492/820) 60.0%, 164 participants are expected to remain in the intervention and 164 in the control group at the 12-week primary outcome measurement. The total baseline completer sample size of N=820 can be taken as a conservative upper bound as the final analyzes will be carried out using GLMM. GLMM takes more information into account and, thus, requires a smaller sample size given the same power.

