**Methods:**

The Untire app study is a waiting list RCT targeting cancer patients and survivors who experience moderate to severe fatigue via social media (Facebook and Instagram) across 4 English-speaking countries (Australia, Canada, the United Kingdom, and the United States). The Untire app includes psychoeducation and exercises concerning energy conservation, activity management, optimizing restful sleep, mindfulness-based stress reduction, psychosocial support, cognitive behavioral therapy, and physical activity. After randomization, participants in the intervention group could access the Untire app immediately, whereas control participants had no access to the Untire app until the primary follow-up assessment at 12 weeks. Participants completed questionnaires at baseline before randomization and after 4, 8, 12, and 24 weeks. The study outcomes are fatigue (primary) and quality of life (QoL; secondary). Potential moderators and mediators of the hypothesized treatment effect on levels of fatigue and QoL were also assessed. Link clicks and app activation are used to assess reach and uptake, respectively. Log data are used to explore the characteristics of app use. Sample size calculations for the primary outcome showed that we needed to include 164 participants with complete 12-week measures both in the intervention and the control groups. The intention-to-treat approach is used in the primary analyses, which refers to analyzing all participants regardless of their app use.

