### Main Analyses

#### Does the Untire App Reduce Fatigue Significantly After 12 Weeks of App Access?

To examine a treatment effect of the app on fatigue, the data collected via Questback’s Web-based survey of fatigue severity and interference will be analyzed using General Linear Mixed Models (GLMM) for 4 repeated measures (baseline, 4 weeks, 8 weeks, and 12 weeks), and 2 groups (intervention and control), following the intention-to-treat (ITT) approach. The ITT approach refers to analyzing all participants, regardless of app use, and is the primary approach in all outcome analyses. Assumptions of linearity, homogeneity of variance as well as the normal distribution of residuals of the model will be tested. The individual measures of fatigue ratings over time (level 1) are nested within each patient (level 2). The default GLMM model without a country factor will be compared with a model with a country factor concerning the best model fit using the Bayesian information criterion.

On the basis of previous studies testing health-related apps targeting behavior [34-39], we estimated the percentage of participants that would lose interest in the app or study assessments, and, therefore, would be lost to follow-up (eg, the 12-weeks measurement), at 60%. For the data analysis, we will, therefore, employ a model that can take missing data into account (ie, GLMM). A comparison of the outcomes of the model run in the ITT approach and the outcomes of a model run among those who have completed at least the 12-week assessment (T12-completers) will demonstrate the robustness of the findings.

In addition to the model validation, we will carry out sensitivity analyses to determine whether the duration and the degree of app use are related to the degree of change in fatigue severity and interference over time. Outcomes of active users will be compared with less-active users. Active and less-active users are categorized according to the duration and degree of app use. The dose-response relationship of app use and treatment effects will be explored in a three-way interaction (time×group×activity level), using GLMM.

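### The stated effect size η²=0.10 does not give the planned 328 completers; Cohen's f=0.10 does, so f was very likely reported as η²

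*Protocol article*

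**What the plan says.** The Sample Size section states that "we needed to include 164 participants with complete 12-weeks measures in the intervention and the control group (total N=328"), and that this number serves "to detect a between-group difference in change from baseline to 12 weeks" "with a minimal effect size of η^2^=0.10", with alpha .05 and power .95. The tool is G*Power 3.1 and the procedure is given as "F tests—repeated measures analysis of variance [with within-between interaction"]. The section adds that "The sample size was calculated using the simplest between/within-group comparison". It then allows for 60% drop-out and arrives at 820 participants at baseline.

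The Abstract repeats the requirement without the effect size: "we needed to include 164 participants with complete 12-week measures both in the intervention and the control groups".

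The section gives no Cohen's f, no correlation between the repeated measures and no number of measurements for the calculation. The main-analysis section confirms "2 groups (intervention and control").

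**The concern.** G*Power's effect-size input for this procedure is Cohen's f, and η² has to be converted to f first. The two are easily confused when the number is 0.10: η²=0.10 is f=0.333, while f=0.10 is η²=0.0099. A total of 328 is far more than an effect of η²=0.10 should need at 95% power.

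This is the only target effect stated for the primary outcome. With the wrong metric, a reader is told that the trial was designed around a larger effect than its size implies. Anyone who re-runs the calculation from the stated inputs gets a much smaller number and cannot see why 820 people were planned.

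**Working it through.** **Inputs from the Sample Size section:** alpha 0.05; power 0.95; η²=0.10; repeated-measures ANOVA, within-between interaction; 164 per group, equal groups, N=328. Number of groups k=2, from the main-analysis section.

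**Inputs assumed because they are not stated:** number of measurements m=2 (baseline and 12 weeks, suggested by the stated contrast and by the description of the comparison as the simplest one), with 4 and 5 also tried; correlation ρ=0.5, with 0 to 0.8 also tried; sphericity.

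**Formulas.** Effect size f² = η²/(1−η²). Noncentral F with df1=(k−1)(m−1), df2=(N−k)(m−1), and noncentrality on G*Power's default scale λ = f²·N·m/(1−ρ). N is raised in steps of 2 until power reaches 0.95.

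**Step 1: the stated effect.** f² = 0.10/0.90 = 0.111, so f = 0.333. Total N needed:

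| m | ρ=0 | 0.3 | 0.5 | 0.7 | 0.8 |
|---|---|---|---|---|---|
| 2 | 62 | 44 | 32 | 20 | 14 |
| 4 | 40 | 30 | 22 | 14 | 10 |
| 5 | 36 | 26 | 20 | 12 | 10 |

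If η²=0.10 is instead the partial η² of the interaction F test, m=2 gives:
- 122 with λ = f²·(N−k)(m−1)
- 120 with λ = f²·N·(m−1)

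Halving alpha to .025 raises the answer only to 38 (default scale) or 142 (partial η²). The between-group main effect needs 90 (m=2) or 76 (m=4).

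No correlation can rescue the figure. For N=328 to have exactly 95% power, λ must be 13.07. With f²=0.111 and m=2 this requires 1−ρ = 0.111 × 328 × 2 / 13.07 = 5.58, but 1−ρ cannot exceed 2. At N=328, m=2 and ρ=0.5, λ for η²=0.10 is 0.111 × 656 / 0.5 = 145.8, and power is practically 1.

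**Step 2: reproducing 328.** With f=0.10, m=2, ρ=0.5, λ = 0.01 × 328 × 2 / 0.5 = 13.12. Power is 0.9507 at N=328 and 0.9495 at N=326, so 328 is the smallest even total. It matches the plan exactly. With the same f and ρ, m=4 gives 216 and m=5 gives 188.

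**Step 3: size of the discrepancy.**
- Default scale: f=0.10 is η² = 0.01/1.01 = 0.0099, and 0.10/0.0099 = 10.1.
- Partial η² of the interaction test: N=328 detects 13.07/(13.07+326) = 0.039, and 0.10/0.039 = 2.6.
- SD of the change score, two equal groups: N=328 detects 2·√(13.07/328) = 0.40. A partial η² of 0.10 corresponds to 2 × 0.333 = 0.67.
- SD of the raw score: multiply 0.40 by √(2(1−ρ)). This gives about 0.57, 0.47, 0.40, 0.31 and 0.25 for ρ = 0, 0.3, 0.5, 0.7 and 0.8.

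**Step 4: inflation.** 328/(1−0.60) = 820, as the plan states. This part is correct.

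**The case against.** The strongest objection is that the explanation is a deduction. The article never mentions f, two measurements or a correlation of 0.5. Other settings could also lead to 328: with f=0.10 and four measurements, N falls from 432 at ρ=0 to 302 at ρ=0.3, so some correlation in between would serve. This stands, and the mislabelling should be called very likely, not proven. It does not touch the main point, because the failure of η²=0.10 to give 328 holds for every setting and convention tried.

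The second objection concerns size. A reader might infer that the trial is ten times over-sized, or that the plan claims an implausible difference in change of 1.33 SD (from f = D/(4·SD) for a 2×2 interaction, so D = 4 × 0.333). Both figures hold only on G*Power's default scale, and 1.33 is in raw-score SD. Read as partial η², the gap is 0.10 against 0.039, or 0.67 against 0.40 SD of the change score, and N=328 is about 2.7 times the 120 to 122 needed. The article does not say which scale was meant, so neither extreme can be given alone.

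The third objection is that nothing in the trial turns on this number. That is largely right. The mixed-model analyses of fatigue and quality of life do not use η² as a criterion, recruitment is complete, and 328 exceeds every number that η²=0.10 requires.

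**Conclusion.** The point holds. The stated effect size and the stated N cannot both be right: η²=0.10 needs 32 completers on G*Power's default scale with two measurements and ρ=0.5 (14 to 62 for ρ from 0.8 to 0), or about 120 to 122 as partial η², and in no case 328. The exact match at f=0.10, two measurements and ρ=0.5 makes it very likely that f was reported as η². The declared detectable effect is then too large by about 10-fold or about 2.6-fold, depending on the scale.

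Two further inferences are not supported. The trial is not underpowered for the effect it names; the error runs the other way. Nor does 0.40 SD become a yardstick for the observed result. It is the effect that 164 completers per group would detect with 95% power, which is not a threshold of relevance, and the article sets no such rule. The 0.40 is independent of the correlation only when expressed in SD of the change score.

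**What to change.** Check the saved G*Power inputs and replace the η² statement with the metric actually entered. If the inference is confirmed, the sentence would read along these lines: Cohen's f=0.10 (η² about 0.01), two measurements, assumed correlation 0.5, that is, a between-group difference of about 0.40 SD of the change score. Add that in raw-score SD this is about 0.57 if the correlation is 0 and about 0.25 if it is 0.8.

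If the record shows that η²=0.10 was really intended, restate the required number of completers, or the power at 328, and say which convention for η² applies.

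The cost is one corrected sentence. Enrolment, drop-out inflation and analysis stay as they are.

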#### Randomization and Blinding

Participants who completed the baseline questionnaire were randomized 2:1 by the Web-based academic survey tool (ie, Questback) into the intervention and control groups. The randomization ratio was chosen for two reasons. First, we expected that intervention participants were less likely to complete the 12-weeks assessment after receiving the incentive for participation (ie, the free access to the Untire app) already at baseline, as compared with control participants who received the incentive after completing the 12-weeks measure. The 2:1 randomization increased the likelihood of a balanced number of completed 12-weeks measures. Second, in case the drop-out rate in the intervention group was higher than expected at the 12-weeks measures, it was considered convenient to have large enough numbers in the intervention group for in-depth app use analyses. Due to the character of the intervention, it was not possible to blind participants and assessors to intervention or control allocation.

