## Results

Throughout March and October 2018, patients with cancer and survivors (N=1137) were eligible and gave consent to participate in this trial. Of these, 847 participants started with the baseline questionnaire and were randomized into two conditions, following a 2:1 randomization with 545 participants assigned to the intervention group and 302 participants assigned to the control group. The last participants completed their 24-week assessment in March 2019.

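### The sample size section assumes 410 per arm, but the trial randomises 2:1; with the only stated drop-out rate, 820 participants give about 219:109 completers, not 164:164.

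*Protocol article*

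**What the plan says.** All references are to the protocol article.

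- **Sample Size.** The requirement is 164 completers per arm (328 in total) "to detect a between-group difference in change from baseline to 12 weeks with a minimal effect size of η^2^=0.10" ("alpha=.05, 1−beta=.95"), from a repeated-measures ANOVA interaction in G*Power. The recruitment target follows: "With the inclusion of 820 participants (410 intervention participants; 410 control participants) and an estimated drop-out of (492/820) 60.0"%, with 164 expected to remain in each arm. The section adds that 820 "can be taken as a conservative upper bound", because the mixed model uses more information.
- **Randomization and Blinding.** "Participants who completed the baseline questionnaire were randomized 2:1". The first reason given is that "we expected that intervention participants were less likely to complete the 12-weeks assessment"; the ratio is meant to make balanced completer numbers more likely.
- **Main Analyses.** One loss-to-follow-up figure, 60%, not split by arm.
- **Results.** 847 were randomised: "545 participants assigned to the intervention group and 302 participants assigned to the control group".

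**The concern.** The sample size paragraph and the randomisation paragraph describe different designs. One enrols equal arms and, by going from 410 to 164 in both, applies the same 60% loss to each. The other enrols two to one because it expects loss to differ by arm. No section reconciles them.

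Two things are at stake. First, the per-arm completer numbers and the power stated for the primary outcome do not follow from the allocation used together with the only drop-out rate given. Second, a reader who sets 302 randomised controls against a planned 410 could conclude that control recruitment fell short, when the gap comes largely from the allocation ratio.

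**Working it through.** **Inputs from the document.** Alpha 0.05, power 0.95, effect 0.10, 328 completers, 820 included, 60% loss, allocation 2:1, achieved 545:302.

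**Inputs assumed.** Two measurements (m = 2), because the section speaks of change from baseline to 12 weeks; correlation ρ = 0.5; and 0.10 read as Cohen's f. The document gives neither m nor ρ.

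**1. Reproduce the plan's figure.** The noncentrality parameter is λ = f² · N · m/(1−ρ) · 4n₁n₂/N², referred to F(1, N−2).
- With f = 0.10, m = 2, ρ = 0.5: f² · m/(1−ρ) = 0.01 × 2/0.5 = 0.04. This equals a standardised difference of 0.40 on the change score, since λ = N·d²/4 for equal arms.
- 164:164: λ = 0.04 × 328 = 13.12, power 95.1%. The smallest even N reaching 95% is 328, as stated.
- Drop-out: 328/0.40 = 820 and 164/0.40 = 410. So the plan's figures reproduce, but only at 1:1 with 60% lost in each arm.
- The effect-size label does not fit. η² = 0.10 taken literally is f = √(0.10/0.90) = 0.333, which needs about 32 completers under the same settings, not 328. With f = 0.10 and m = 2, N runs from 652 at ρ = 0 to 198 at ρ = 0.7.

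**2. Apply the trial's allocation.**
- 820 × 2/3 = 546.7 and 820 × 1/3 = 273.3, so about 547:273.
- 60% lost in each arm: 546.7 × 0.40 = 218.7 and 273.3 × 0.40 = 109.3, so about 219:109. Controls are 164 − 109 = 55 below the stated requirement, about one third.
- Allocation factor: 4 × 219 × 109/328² = 0.8875. λ = 13.12 × 0.8875 = 11.64, power about 92.5%.

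**3. Let drop-out differ in the expected direction, with 60% lost overall.**

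| Loss, intervention / control | Completers | Power |
|---|---|---|
| 60% / 60% | 219:109 | about 92.5% |
| 65% / 50% | 191:137 | 94.5% |
| 70% / 40% | 164:164 | 95.1% |

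The last row is the only split that yields 164:164 from 820 at 2:1: 1 − 164/546.7 = 0.70 and 1 − 164/273.3 = 0.40.

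**4. Achieved numbers, for orientation.** 545:302 with 60% lost in each arm is about 218:121, power 94.0%.

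**5. Does the allocation undo the upper-bound sentence?** Take a mixed model on four visits with compound symmetry, assumed retention of 75%, 55% and 40% at weeks 4, 8 and 12 in both arms, and a raw difference of 0.40 SD. Compare it with the 164:164 completer analysis at the same correlation.

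| ρ | Mixed model, 547:273 | Completers, 164:164 |
|---|---|---|
| 0.5 | 96.8% | 95.1% |
| 0.3 | 90.9% | 86.3% |

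At both correlations the mixed model at 2:1 exceeds the stated completer calculation.

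**The case against.** The strongest defence is that 60% is written as an overall figure (492/820), that 2:1 was chosen precisely to equalise completers, and that 164:164 is therefore what the design aims at. The aim is indeed stated. But the section does not calculate it: it enrols 410 per arm, and under the expected heavier intervention loss that would not leave equal completers.

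It is also fair that the loss of power is small, that the completer ANOVA is not the primary analysis, and that the powers above depend on an effect-size reading the document does not state. With η² = 0.10 taken literally, power at 219:109 would be essentially 100%, but then 328 would not be the required number either. These points limit the weight of the finding; they do not remove the contradiction.

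Three stronger readings are tempting and are not supported:

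- **That the upper-bound claim falls with the allocation.** A reader might set 90.9% at correlation 0.3 against the planned 95%. The 95% holds only at correlation 0.5; at 0.3 the 164:164 analysis itself has 86.3%. The fall comes from changing the correlation, not from 2:1.
- **That the plan secretly assumes 70% and 40% loss.** Those rates are a back-calculation. The document gives a direction of difference and no arm-specific rates.
- **That the trial is seriously underpowered.** Under the stated 60% overall loss and the expected direction, completer power stays between about 92.5% and 95.1% across the splits tabulated.

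**Conclusion.** The point holds, at moderate severity. The sample size section states an allocation the trial did not use. Its per-arm completer numbers do not follow from 2:1 with the only drop-out rate given: about 219:109 replaces 164:164. On completer analysis the cost is about 2.5 percentage points of power (95.1% to about 92.5%) if loss is equal, and less as loss shifts toward the intervention arm, up to the split that balances completers.

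The completer counts need only the document's own figures. The powers rest on Cohen's f = 0.10, two measurements and correlation 0.5, chosen because they reproduce N = 328. The mixed-model comparison also rests on the assumed retention pattern and compound symmetry. No analysis or estimand is affected.

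**What to change.** In the Sample Size section:

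1. Replace 410:410 with the planned 2:1 split of 820, about 547:273.
2. Then choose one of two statements. Either give the arm-specific drop-out rates that lead to 164:164 (about 70% intervention and 40% control) and present them as an assumption; or keep 60% in both arms and give about 219:109 completers with about 92.5% power.
3. Name the effect-size metric, the number of measurements and the correlation, so that N = 328 can be reproduced.

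The upper-bound sentence need not be withdrawn on account of the allocation. Achieved numbers belong in Results, where they already stand; the planning section need not carry power for the achieved sample.

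The cost is a few sentences and one recalculation. Recruitment is closed with 847 randomised, and no extra participants are needed. If the second statement is chosen, the stated power becomes slightly less favourable.

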## Results

Throughout March and October 2018, patients with cancer and survivors (N=1137) were eligible and gave consent to participate in this trial. Of these, 847 participants started with the baseline questionnaire and were randomized into two conditions, following a 2:1 randomization with 545 participants assigned to the intervention group and 302 participants assigned to the control group. The last participants completed their 24-week assessment in March 2019.

## Discussion

### Principal Findings

This protocol describes an RCT to assess the effectiveness of the Untire app in reducing fatigue in patients and survivors of cancer after 12 weeks of app use as compared with a waiting list control group. Substudies nested within this trial include questions concerning the reach and costs of online recruitment and uptake and usage of the Untire app. There are advantages of stand-alone mHealth apps assumed, such as the immediate access to the app, the low thresholds to seek support via an app, and lower costs in supporting patients as compared with therapist-guided treatments.

The Untire app is based on a face-to-face therapy protocol, which was developed by the HDI in the Netherlands [25]. Although successful therapeutic elements have been used continuously over the years (eg, psychoeducation, CBT, physical activity, and mindfulness) [40], new ways of treatment delivery are increasingly being explored. For example, face-to-face treatment protocols have been effectively adapted to fit therapist-guided internet therapy [13]. More recently, the ingredients of the *More fit after Cancer* protocol were used to develop an adapted version in the form of a stand-alone app. The key therapeutic ingredients remained, but no supervision of a therapist is available. Apart from this shift to self-management, the app offers flexibility as the patients are allowed to choose from the entire library of education and exercises instead of following a structured week-by-week program. Although the app includes proven successful therapeutic elements, it is important to test its effectiveness as the delivery mode differs from previously tested interventions. If we do find the app to be effective, it can easily be offered worldwide to patients with cancer and survivors experiencing fatigue.

The findings will not only show whether or not the app is effective in reducing fatigue and improving QoL but will also provide more insight into the underlying mechanisms. Several routes may lead to a reduction in fatigue. For example, participants may gain vitality through improvements in the quality of their sleep, increases in physical exercise, and better management of their physical activities (eg, balancing activities throughout the day) [13]. Participants may also improve because they learn to better manage their unhelpful or catastrophizing thoughts about their fatigue, possibly through mindfulness [13]. Previous diary research has shown that such catastrophizing thoughts are associated with increases in negative affect and fatigue during the day [41]. This study will demonstrate whether improvements in these factors mediate hypothesized improvements in fatigue. Patients with specific problems concerning sleep or physical activity, or with respect to unhelpful and catastrophizing thoughts may benefit specifically from improvements in the respective areas.

